### Study variables

2.3

The main variable of this study is the variation of seric concentration levels of IL6 at randomization and on days 1, 3, 5, 21 post-surgery in esophagectomized patients receiving fish-oil lipid emulsions parenterally for 5 days compared with those receiving LCT/MCT emulsions.

The secondary variables will examine whether intravenous administration of fish-oil lipid emulsions instead of LCT/MCT for 5 days leads to differences from randomization and on days 1, 3, 5 and 21 post-randomization with respect to:

Seric concentrations of inflammatory markers: RCP, TNF-α, IL-10, IL-8 and soluble interleukin-2 receptor.Morbidity measured as post-operative complications: suture dehiscence, chylotorax, pneumonia and other infections.Safety measured as hepatic impairment (total bilirubin, alanin-aminotranspherase, aspartate-amino transpherase, gammaglutamil transpherase, alkaline phosphatase) and alteration in coagulation parameters (INR, prothrombin time, platelet count).Nutritional parameters: albumin, prealbumin and lymphocytes.Mortality measured for a year after surgical intervention.

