**Materials and methods::**

Prospective, single-center, randomized, double-blind study in esophagectomized patients, and treated after surgery with parenteral lipid emulsions of ω-3 fatty acids or a mixture of ω-6 long-chain triglycerides/short-chain triglycerides 50%. These emulsions will be added to the standard nutritional support in continuous infusion until 5 days of treatment have been completed. Patients will be randomized 1:1:1 in Group A receiving 0.4 g/kg/d of fish-oil lipid emulsion and 0.4 g/kg/d of a lipid emulsion mixture of ω-6 long-chain fatty acids (LCT) plus medium-chain fatty acids (MCT) (total dose of 0.8 g/kg/d of lipid emulsion); Group B receiving 0.8 g/kg/d of fish oil lipid emulsion and Group C receiving 0.8 g/kg/d of LCT/MCT emulsion.

The main objective is to determine whether 5 days administration of intravenous ω-3 fatty acid lipid emulsion is effective in normalizing interleukin-6 levels compared with LCT/MCT emulsions, and whether a 0.8 g/kg/d dose is more effective than 0.4 g/kg/d. Secondary outcomes include other inflammatory markers such as C-reactive protein, tumor necrosis factor alpha and interleukin-10, and parameters of morbidity, safety, nutrition and mortality.

Samples will be collected at the time when surgery is indicated and on days 0, 1, 3, 5 and 21 to determine inflammatory, nutritional, hepatic and safety parameters. In addition, clinical follow-up will be continued throughout the hospital admision and up to 1 year after surgery.

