#### Patients recruitment, randomization and allocation

2.2.2

All patients allocated for EPG following medical criteria, and those who meet the inclusion criteria will be candidates to participate in the trial.

The surgical team will be responsible for communicating the possibility of participating in this trial when IC is obtained for the surgical intervention. IC for participation in this trial will be collected before randomization.

Subjects will be randomized to 3 groups (1:1:1) by a pharmaceutical researcher after recruitment by the surgical team:

Group A will receive 0.4 g/kg/d of fish-oil LE and 0.4 g/kg/d of a LE mixture LCT/MCT receiving a total dose of 0.8 g/kg/d of LE over 5 days post-surgery,Group B will receive 0.8 g/kg/d of fish-oil LE,And Group C will receive 0.8 g/kg/d of a LE mixture of LCT/MCT 50%.

This allocation will be blind for all patients and health personnel. The allocation sequence (computer-generated random numbers) will be generated by the pharmaceutical researcher and it will be performed by randomized blocks permutated with the block size defined at random. In the first step, blocks of size 3 with possible sequences ABC, ACB, CAB and CBA, and size 6 will be defined. In a second step the clusters will be randomized, and in a third step the sequences will be randomized within the blocks. This method ensures that the groups are balanced throughout the study, and that the researcher cannot predict the sequence. The pharmaceutical researcher will be responsible for patient assignation to the corresponding intervention group, and will also assign a numbered patient identification code for each patient in the trial. The composition of the emulsion administered to each patient will only be known by: the pharmaceutical researcher responsible for clinical trials, the pharmaceutical researcher who will validate its conduct, and the personnel who will conduct it.

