##### Analytical data

2.5.1.1

-Inflammatory parameters: values of IL-6, RCP, TNF-α, IL-10, IL-8 y CD25 on days 0, 1, 3, 5 and 21 post-surgery will be recorded. These values have been selected according to what is reported in the literature in similar studies.^[19–25]^ Also, these same values will be recorded pre-operatively at the time surgical intervention is indicated to show the patient's baseline inflammatory status.-Nutritional parameters: albumin, prealbumin and lymphocytes at the time surgical intervention is indicated and on days 0, 1, 3, 5 and 21.-Hepatic parameters: total bilirubin, alanin-aminotranspherase, aspartat aminotranspherase, gammaglutamil transpherase and alkaline phosphatase at the time surgical intervention is indicated and on days 0, 1, 3, 5 and 21.-Safety: INR, prothrombin time and platelet count at the time surgical intervention is indicated and on days 0, 1, 3, 5 and 21.

The total number of blood extractions per patient will be 6.

Clinical data: the following data will be recorded:

-Post-surgery complications such as chylothorax, dehiscence, pneumonia and other infections.-Mortality: from the day of surgery to 1 year following surgery.-Nutritional support: the amount of EN received by each patient will be recorded to determinate total calories administered.

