#### Statistical analysis

2.6.1

Descriptive statistics will be employed for all collected variables data, such as baseline values for inflammatory, nutritional, hepatic and safety parameters, in frequency tables. For continuous variables, statistical descriptions will be used (n, average, standard deviation, value range and median), meanwhile grouped percentages will be used for categorical variables.

The main objective is to establish the difference between basal values of inflammatory parameters and values at day 5 post-randomization, and to assess differences between days 1, 3 and 21. The secondary objectives are to establish the difference between basal values of morbidity, safety and nutritional parameters and those values at day 5 post-randomization.

Significance will be calculated using Student's *t* test for matching data or Wilcoxon-test (non-parametric test) depending on whether normality can be assumed or not. To establish the differences among the 3 groups for the same period of time, Student's *t* test (parametric test) or Mann Whitney *U* test (non-parametric test) will be used, depending on whether normality can be assumed or not. For categorical variables, the chi-square test or the Fisher test will be used when necessary.

The significance level will be established with a 95% confidence interval (CI). Data will be processed with SPPS v 19.

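### The primary IL-6 endpoint has two time zeros and no single named baseline sample, so the reference value for the day-5 comparison is not fixed

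*Protocol article*

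**What the plan says.** The protocol article gives the timing of the primary measurement in several places.

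- **Study variables (2.3), main variable:** the "variation of seric concentration levels of IL6 at randomization and on days 1, 3, 5, 21 post-surgery". The reference is randomisation and the later days run from surgery.
- **Study variables (2.3), secondary variables:** the question is whether treatment "leads to differences from randomization and on days 1, 3, 5 and 21 post-randomization with respect to" the other markers and outcomes. The day numbers are the same, counted from randomisation.
- **Statistical analysis (2.6.1):** the main objective is the "difference between basal values of inflammatory parameters and values at day 5 post-randomization". The reference is an undefined basal value and the clock is randomisation.
- **Analytical data (2.5.1.1):** IL-6 and the other markers "on days 0, 1, 3, 5 and 21 post-surgery will be recorded". In addition, "these same values will be recorded pre-operatively at the time surgical intervention is indicated", and this sample is the one said to show baseline inflammatory status. The stated total is six blood draws per patient.
- **Patients recruitment, randomization and allocation (2.2.2):** the surgical team is responsible for "communicating the possibility of participating in this trial when IC is obtained for the surgical intervention". Randomisation follows recruitment, with no day given.

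The Abstract asks whether fish oil is "effective in normalizing interleukin-6 levels compared with LCT/MCT emulsions". Study objectives (2.1) speaks of reducing inflammation for the main comparison and of normalisation for the dose comparison.

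**The concern.** The variable definition and the analysis section use different clocks for the same endpoint. Patients are approached before the operation and randomised at some later, unstated moment. If that moment is before the day of surgery, day 5 after randomisation is not day 5 after surgery, and it need not coincide with any scheduled draw.

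The reference value is also open. It could be a sample at randomisation, an undefined basal value, or the pre-operative sample. There is also a day-0 draw that may or may not be the same as one of these. The Abstract describes a marked inflammatory response to this surgery, so samples taken before and after the operation are not interchangeable. If the baseline is not fixed before unblinding, the change tested within patients and the precision of the arm comparison both depend on a later choice.

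**Working it through.** **1. Side by side**

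| Place | Reference value | Days counted from |
|---|---|---|
| 2.3, main variable | randomisation | surgery |
| 2.3, secondary variables | randomisation | randomisation |
| 2.6.1, main analysis | basal, undefined | randomisation |
| 2.5.1.1, sampling | pre-operative draw (called baseline) and day 0 | surgery |

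Sample count: 1 pre-operative + 5 (days 0, 1, 3, 5, 21) = 6, which agrees with the stated total. All six are accounted for and none is labelled as the randomisation draw. There is only one day-5 sample, so the real choice is which earlier sample it is compared with: pre-operative or day 0.

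**2. Within-patient change.** The documents give no IL-6 values. These ranges (pg/mL) are assumptions for illustration: pre-operative 3 to 10; day 5 of 20 to 40 in control and 10 to 25 in treated patients.

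| Baseline used | Control, change to day 5 | Treated, change to day 5 |
|---|---|---|
| Pre-operative, 3 to 10 | 20−10 = +10 to 40−3 = +37 | 10−10 = 0 to 25−3 = +22 |
| Day 0 after surgery, 50 to 200 | 40−50 = −10 to 20−200 = −180 | 25−50 = −25 to 10−200 = −190 |
| Day 0 before surgery, 5 | 20−5 = +15 to 40−5 = +35 | 10−5 = +5 to 25−5 = +20 |

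The sign reverses only if day 0 is drawn after the operation and lies above day 5.

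**3. Between-arm difference in change.** (day 5 treated − baseline) − (day 5 control − baseline) = day 5 treated − day 5 control, when both arms share the same expected baseline. That is 25−40 = −15 or 10−20 = −10, whichever pre-treatment baseline is used.

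**4. Precision.** The stated size is 33 patients for 80% power, 5% alpha and 10% losses (2.2.3). It cannot be reproduced, because no difference, SD, time point or sidedness is given. Working back, and taking 33 as the total over three arms: 33 × 0.9 = 29.7, about 10 per arm. The two-sided implied effect is (1.960 + 0.842) × √(2/10) = 1.25 SD. I use 1.26 SD, the smallest rounded value that gives n = 10 per arm.

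With correlation ρ between baseline and day 5 and equal SDs (both assumed):

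- change score: relative SD = √(2(1−ρ))
- baseline-adjusted: relative SD = √(1−ρ²)
- power = Φ(1.26 / (relative SD × √(2/10)) − 1.960)

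| ρ | Relative SD, change | Power, change | Relative SD, adjusted | Power, adjusted |
|---|---|---|---|---|
| 0 | 1.414 | 0.513 | 1.000 | 0.804 |
| 0.2 | 1.265 | 0.605 | 0.980 | 0.820 |
| 0.5 | 1.000 | 0.804 | 0.866 | 0.902 |
| 0.8 | 0.632 | 0.994 | 0.600 | 0.997 |

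The pre-operative and day-0 samples may correlate differently with day 5, so the choice between them moves along this table. The adjusted analysis is much less sensitive to that choice. These are normal approximations and slightly optimistic at 10 per arm.

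**The case against.** The strongest reply is that the text supports one schedule. The main variable's list (randomisation, then days 1, 3, 5, 21) lines up item by item with the sampling list (days 0, 1, 3, 5, 21). If randomisation is day 0, the clocks coincide and *basal* means the day-0 sample. The pre-operative draw is introduced as an addition and can be read as descriptive. The two figures are not shown and may give the timing, and a fuller protocol or analysis plan may exist.

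Much of this stands. The day-0 reading is plausible, and it reduces the candidates to two samples. But section 2.2.2 never places randomisation on the day of surgery, the only sample called baseline is the pre-operative one, and a figure would not remove the conflicting wording in 2.3 and 2.6.1.

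A reader might also infer that the direction of the trial's main result depends on the baseline. The documents do not support that. The objective compares arms, and step 3 shows that the expected difference does not change with the pre-treatment baseline. Only the paired within-patient result can reverse, and that needs IL-6 values and a post-operative day 0 that the documents do not state. Nor do they show that day 5 after randomisation falls before treatment in any patient; the text merely does not exclude it.

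**Conclusion.** The inconsistency is real and concerns the primary endpoint, so it should be resolved before unblinding. The main variable and the sampling schedule count from surgery; the main analysis counts from randomisation, against an undefined reference. The timing of day 0 relative to the operation and the first infusion is not stated.

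The consequence is moderate. The within-patient change could differ and possibly reverse. The expected between-arm difference would not, provided the chosen baseline precedes treatment and change is taken as a simple difference. Its precision would: under the assumptions above, change-score power at the planned size lies between 51% and 99%. In a 33-patient trial that could decide significance.

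The mixed use of normalising and reducing IL-6 is a secondary point. Section 2.6.1 tests only differences and defines no normal value.

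**What to change.** 1. Count all days from surgery, as the sampling schedule already does, and replace the post-randomisation wording in 2.3 (secondary variables) and 2.6.1.
2. State when the day-0 sample is drawn relative to the operation and the start of infusion. This must be established from what was actually done, since recruitment began in 2018 (Trial status) and past draws cannot be re-timed.
3. Name one pre-treatment sample as the primary baseline before unblinding: day 0 if it was drawn before the infusion, otherwise the pre-operative sample. Use that name in 2.3, 2.5.1.1 and 2.6.1.
4. Make the primary analysis the between-arm comparison of IL-6 at day 5 after surgery, adjusted for that baseline. Keep the paired within-arm tests as descriptive.
5. Align *normalizing* in the Abstract and in the dose objective (2.1) with the reducing objective, or define it.

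The cost is an amendment of wording plus a small change of analysis, since item 4 replaces the Student's t or Mann-Whitney comparison in 2.6.1. No extra samples or visits are needed.

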### Study objectives

2.1

The main objective of this study is:

To establish if the endovenous administration of ω-3 fatty-acid fish-oil lipid emulsions for 5 days in esophagectomized patients is effective in reducing inflammation – measured as seric concentration of interleukin-6 (IL-6) – compared to the administration of lipid emulsions of LCT/MCT. Additionally, to determine if doses of 0.8 g/kg/d are more effective than doses of 0.4 g/kg/d in the normalization of IL-6.

The secondary objectives aim to determine if the intravenous administration of ω-3 fatty-acid fish-oil lipid emulsions for 5 days in esophagectomized patients shows differences compared with the administration of LCT/MCT lipid emulsion with regard to:

Seric concentration of other inflammatory parameters: C-reactive protein, tumoral necrosis factor-α (TNF-α), interleukin-10 (IL-10), interleukin-8 (IL-8) and soluble interleukin-2 receptor. In addition, in the follow-up, whether these markers, alone or in combination, show equal or greater efficacy of effect on the inflammatory response compared to IL-6.Post-operative complications: suture dehiscence, chylotorax, pneumonia and other infections.Safety, measured as hepatic impairment and alterations in coagulation parameters.Nutritional parameters: albumin, prealbumin and lymphocytes.Mortality: evaluated at hospital admission and at 1 year post-surgical intervention.

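### The protocol does not state that IL-6 at day 5 alone decides the primary result: days 1, 3 and 21 share the main variable and the main objective

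*Protocol article*

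**What the plan says.** Three sections of the protocol article bear on when the primary result is read.

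- **2.1 Study objectives** gives no assessment day. The five days mentioned there are the length of the infusion: the question is whether giving the emulsion "for 5 days in esophagectomized patients is effective in reducing inflammation".
- **2.3 Study variables** defines the main variable as the "variation of seric concentration levels of IL6 at randomization and on days 1, 3, 5, 21 post-surgery". No day is singled out and no summary over days is defined.
- **2.6.1 Statistical analysis** opens its main objective with day 5: "The main objective is to establish the difference between basal values of inflammatory parameters and values at day 5 post-randomization". The same sentence continues "and to assess differences between days 1, 3 and 21". The secondary objectives have a sentence of their own, and days 1, 3 and 21 do not appear in it.

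For the between-group comparison, 2.6.1 names a t test or Mann-Whitney test "To establish the differences among the 3 groups for the same period of time", that is, one test per period, with significance judged against a 95% confidence level. Section 2.2.3 sizes the trial at 33 patients for 80% power, 5% alpha and 10% losses. It does not say which IL-6 day the calculation used.

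**The concern.** The section that defines the main variable treats four post-operative days alike. The section that analyses it leads with one of them but does not demote the others. Two careful readers could come away with different primary endpoints.

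The days are not interchangeable. Day 1 falls early in the 5-day course, day 5 around its end, and day 21 more than two weeks later. If the results disagree across days, the protocol does not say whether the trial has met its main objective. Because the groups are tested separately at each period, the stated 5% alpha is secured only if one day is fixed in advance as the one that counts.

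**Working it through.** **The plan's own figure.** The 33 patients cannot be reproduced, because no difference, SD or IL-6 day is given. The allowance for losses can be checked: 30 × 1.10 = 33, and 29 / 0.90 = 32.2, rounded up to 33. Either way about 30 patients are evaluable, so about 10 per arm under 1:1:1 allocation. The figure of 10 is derived, not stated.

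**Inputs**
- Four post-operative days: 2.3.
- One test per period at 5%: 2.6.1. Two-sided testing is assumed, as sidedness is not stated.
- 10 evaluable patients per arm: derived above.
- Correlation between days: not in the document. It is assumed equal for all pairs of days and varied from 0 to 0.9.

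**Independent days.** Chance of at least one false-positive day = 1 − 0.95⁴ = 1 − 0.8145 = 18.5%.

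**Correlated days.** 40,000 simulated trials with no true effect, normal responses, 10 per arm, and a two-sample t test (18 degrees of freedom) on each of four days for one pair of arms:

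| Assumed between-day correlation | At least one of four days significant | Day 5 alone |
|---|---|---|
| 0 | 18.5% | 5.0% |
| 0.3 | 17.6% | 5.1% |
| 0.5 | 16.0% | 5.0% |
| 0.7 | 13.4% | 4.8% |
| 0.9 | 9.5% | 5.0% |

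**Which part of the range is plausible.** The variable is a change from a shared baseline. Suppose baseline and all later days have variance σ² and common correlation ρ. Two change scores then have covariance σ²(1 − ρ) and variance 2σ²(1 − ρ), so their correlation is 0.5 whatever ρ is. That points to about 16%. Unequal variances would move it, so this too is an assumption.

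**Keeping all four days primary instead.** A Bonferroni split gives 0.05 / 4 = 0.0125 per day. The document gives no effect size, so one is back-solved: with 10 against 10, 80% power at two-sided 5% needs a standardised difference of 1.32 (t test). At 0.0125 the power for that difference falls to 58%. Restoring 80% takes 15 per arm, 45 in all, and 45 / 0.90 = 50 with losses, against the 33 planned.

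**The case against.** The best case for the plan is that day 5 is already primary in substance. Section 2.6.1 names it first and gives it its own clause; the other days follow with a weaker verb; the secondary objectives are tied to day 5; and day 5 matches the end of the infusion. The list in 2.3 could then be read as a sampling schedule, since the same days recur for the secondary variables. On that reading a single contrast keeps its 5% error rate. This is a fair reading and probably the intended one. But 2.3 is where the main variable is defined and it gives day 5 no priority, while 2.6.1 leaves the other days inside the main objective. The text supports the reading without fixing it.

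A second objection is that a separate analysis plan, not shown, may settle multiplicity and modelling. It may, and the absence of those details is not the complaint. What remains is that two protocol sections describe the main endpoint differently, alongside a period-by-period testing rule that the protocol itself states.

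Two stronger readings are tempting and should be resisted. A reader might infer that the trial plans to report whichever day turns out significant. No section says so; the wording leaves that open but does not announce it. A reader might also quote the error over all three pairs of arms and four days, about 41% to 22% over the same correlations. That figure mixes in the number of arm contrasts, which is a separate issue: with day 5 fixed, three pairs alone give about 12%.

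**Conclusion.** The point holds as an unresolved ambiguity between 2.3 and 2.6.1: day 5 is put forward but is not stated to be the sole deciding time point. The loss of the 5% alpha is conditional on any of the four days being allowed to count. In that case the chance of a false-positive day for one pair of arms is about two to four times nominal: 18.5% down to 9.5%, and about 16% at a correlation of 0.5. These figures rest on 10 evaluable patients per arm, two-sided tests, normal responses and equal between-day correlations, none of which the document states directly. The inflation exceeds 5% at every correlation examined. Confidence is high for the ambiguity. The document does not support any claim that the day will in fact be picked after the data are seen.

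**What to change.** In 2.3 and 2.6.1, state in the same words that the single confirmatory time point is day 5, through the between-group comparison of change in IL-6 from baseline to day 5. Label days 1, 3 and 21 as supportive, reported as estimates with confidence intervals. Count the days from one origin in both places, since 2.3 counts from surgery and 2.6.1 from randomization.

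The tests already named can serve for the day-5 comparison. A repeated-measures model over all days is an optional way to obtain the same contrast. With about 30 patients it would need a small-sample correction, and a transformation of IL-6 if it is skewed, because the model replaces the non-parametric fallback that 2.6.1 provides.

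The cost is a sentence in each section, with no extra patients or samples. The downside is that a difference seen only on day 1, 3 or 21 could no longer be claimed as the primary result. How many arm contrasts are confirmatory needs its own decision and is not settled by this change.
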